## Abstract

**Background:**

Most people with dementia (PwD) are cared for at home, with general practitioners (GPs) playing a key part in the treatment. However, primary dementia care suffers from a number of shortcomings: Often, diagnoses are made too late and therapies by GPs do not follow the guidelines. In cases of acute crises, PwD are too often admitted to hospital with adverse effects on the further course of the disease.

The aim of this study is to implement and evaluate a new GP-based, complex dementia care model, DemStepCare. DemStepCare aims to ensure demand-oriented, stepped care for PwD and their caregivers.

**Methods/design:**

In a cluster randomized controlled trial, the care of PwD receiving a complex intervention, where the GP is supported by a multi-professional team, is compared to (slightly expanded) usual care.

GPs are clustered by GP practice, with 120 GP practices participating in total. GP practices are randomized to an intervention or a control group. 800 PwD are to be included per group. Recruitment takes place in Rhineland-Palatinate, Germany. In addition, a second control group with at least 800 PwD will be formed using aggregated routine data from German health insurance companies. The intervention comprises the training of GPs, case management including repeated risk assessment of the patients’ care situation, the demand-oriented service of an outpatient clinic, an electronic case record, external medication analyses and a link to regional support services. The primary aims of the intervention are to positively influence the quality of life for PwD, to reduce the caregivers’ burden, and to reduce the days spent in hospital. Secondary endpoints address medication adequacy and GPs’ attitudes and sensitivity towards dementia, among others.

**Discussion:**

The GP-based dementia care model DemStepCare is intended to combine a number of promising interventions to provide a complex, stepped intervention that follows the individual needs of PwD and their caregivers. Its effectiveness and feasibility will be assessed in a formative and a summative evaluation.

**Trial registration:**

German Register of Clinical Trials (Deutsches Register Klinischer Studien, DRKS), DRKS00023560. Registered 13 November 2020 - Retrospectively registered. HTML&TRIAL_ID=DRKS00023560.

## Introduction

### Background and rationale

Approximately 50 million people worldwide live with dementia [1, 2]. By 2050, this number is expected to have tripled [3]. When dealing with dementia, outpatient care is of great importance: The majority of people with dementia (PwD) are cared for by family members [4]. However, primary dementia care still faces a number of problems.

#### Provide timely and accurate diagnoses

Some of the problems can be ascribed to general practitioners (GPs), who should often be the first to detect the onset of dementia and deal with it adequately. It has been shown that GPs are often reluctant to face the diagnosis of dementia and do not follow the existing guidelines [5–9]. GPs do not want to “scare off” their patients and they feel that they have little chance to do anything about the disease [10]. Affective factors and experienced self-efficacy are of great importance here, not just the GPs’ previous knowledge and competence [11, 12]. As a result, dementia diagnoses are often not made [13, 14] or only when home care is already at risk. From a therapeutic perspective, however, it has been shown that early diagnosis of dementia is crucial to positively influence the course of the disease [15–17]. A major goal in improving primary dementia care is therefore the timely and accurate diagnosis of dementia.

#### Avoid (medical) errors in therapy

However, not only the diagnostic process needs to be improved. It has been shown that GPs are often overburdened or succumb to a number of misconceptions when it comes to the treatment of dementia [18, 19]. In many cases, the existing guidelines [20, 17] are not followed [21]. For example, there are often errors in the prescription of medicines [22–25]. One difficulty here is that PwD are at higher risk of multimorbidity and polymedication due to their usually older age [26]. Dementia-specific training courses for GPs might be beneficial here [27, 28].

#### Involve and coordinate various healthcare professionals

Other problems of primary dementia care are structural in nature. The complexity of the clinical picture necessitates multi-professional and multimodal care [29, 30]. Needs vary greatly between individuals and over the course of the disease [31], making individualized and stepped interventions necessary. Integrated, cross-sectoral approaches to effective outpatient dementia care are needed [32]. GPs often lack knowledge about existing regional services to support PwD and their caregivers [33]. Studies on case management in dementia care have not yet revealed consistent results [34], but case management seems to be a promising factor that might facilitate the needs-based [35], stepped activation of different healthcare professionals and thus contribute to improving the care of PwD [36].

Furthermore, the different healthcare professionals involved must communicate effectively with each other to ensure continuity of care. There is a lack of efficient (digital) communication structures, especially in rural areas [37]. User-friendly solutions are needed here.

#### Support informal caregivers and avoid hospitalization

Family caregivers are exposed to increased physical and psychological stress [38–41]. This in turn can affect the caregivers’ health [41, 38]. If any additional crises occur, this can lead to hospitalization of the PwD they care for [42]. However, it has been shown that hospitalization of PwD tends to have negative consequences for their health [43] as well as for the caregivers’ emotional stability [44]. In addition, hospital stays are expensive [45] and burden the healthcare system. It is therefore an important objective to avoid unnecessary hospitalization [46], while providing effective support for caregivers.

### Objectives

The study is intended to bundle a number of possibly effective interventions to provide a complex, stepped intervention that follows the individual needs of PwD and their caregivers. DemStepCare seeks to provide structures that improve and stabilize outpatient dementia care. The primary aims of the intervention are as follows: to positively influence the quality of life of PwD, to reduce the caregivers’ burden, and to reduce the days spent in hospital.

Further goals include the improvement of guideline-based diagnostics and therapy, improved safety and quality of drug therapy and increased sensitivity to the topic of dementia, as well as an increased willingness and acceptance of GPs to provide care for PwD. In DemStepCare regional support services are to be used more effectively, risk constellations in home care are to be detected earlier and home care is to be stabilized. In addition, it will be evaluated whether the intervention is cost effective. A process evaluation will be conducted to investigate how the intervention works and to identify factors that hinder its implementation.

### Trial design

In a prospective, cluster randomized trial, two types of primary dementia care will be compared to each other: the innovative complex intervention DemStepCare (intervention group) and a slightly expanded usual care condition (control group 1). In addition, a second (historical) control group will be formed, which will be composed of aggregated routine data from health insurance companies involved in the project (control group 2).

A total of 120 GP practices are to be included for the intervention group and control group 1. Randomization with a 1:1 ratio is undertaken at the level of GPs’ practices and stratified by dementia sensitivity of the GPs. 800 PwD are to be included per group (i.e. intervention group, control group 1, control group 2).

Measurement times for PwD and caregivers are t0 (=time of inclusion) and t1 (=minimum duration of the intervention / nine months after t0). In addition, in the intervention group the further course of treatment is examined longitudinally and included in the evaluation (t2 = end of intervention / max. 27 months after t0).

The design of the study is shown in Fig. 1.

**Fig. 1 Fig1:**
[figure not shown]
Design of the cluster randomized controlled study DemStepCare. t0 = study inclusion, t1 = minimum duration of the intervention, nine months after t0; t2 = end of intervention, max. 27 months after t0

## Methods: participants, interventions, and outcomes

### Study setting

The catchment area of DemStepCare is in a largely rural area of Rhineland-Palatinate, Germany. The outpatient clinic is located in the middle of the recruitment area at Rheinhessen Fachklinik Alzey, Landeskrankenhaus (AöR), allowing all patients of the intervention group to be reached.

Control group 2 will be composed of patients from all over Germany.

### Eligibility criteria

Patients and (if possible) their caregivers are eligible to participate in the intervention group or control group 1, if they meet the following criteria:
Diagnosis of dementiaPlace of residence within the study areaInformed consent to participate in DemStepCare

Living in a nursing home is defined as an exclusion criterion.

As patients can only be included via their GPs, the patients must be cared for by a GP who participates in DemStepCare. The only requirement for participating GPs is that their practice must be within the study area.

### Interventions

#### Description of the intervention condition

The first part of the intervention involves training of the GPs: GPs are to identify dementias earlier and become more confident in dealing with the diagnosis. The training courses impart knowledge about the appropriate diagnosis and treatment of PwD following the guidelines of the German Society for Psychiatry and Psychotherapy, Psychosomatics and Neurology (Deutsche Gesellschaft für Psychiatrie und Psychotherapie, Psychosomatik und Nervenheilkunde, DGPPN) [17].

The so trained GPs enroll patients and if possible their caregivers in the study program. Patients with a pre-existing dementia diagnosis as well as patients who receive a new dementia diagnosis while DemStepCare is running can be included in the study. If there is a suspected dementia, the GPs can either diagnose dementia themselves or refer the patients to a specialist / memory clinic. Patients with a confirmed dementia diagnosis and if possible their caregivers are informed about the study and asked if they are willing to participate. If patients and their caregivers wish to participate, they must give their written consent. If there is a legal guardian, the legal guardian must give written consent in addition to the patient. All patients require a basic competency to consent, otherwise they cannot participate. Having given their written consent, patients are assigned to a case manager who conducts a first counselling interview, including information on regional support options (e.g. a supervised relatives’ group that is part of DemStepCare, counselling centers) and advice on care. At this first encounter, the case manager assesses the individual risk constellation of the home care situation using a dementia specific screening tool (in German: Demenzspezifisches Screening zur Versorgungssituation, DSV [47]). The DSV addresses both aspects concerning the patient and aspects concerning the caregiver. When evaluating the DSV, there are two possible results: green (stable situation) or yellow (increased risk). In the case of an increased risk, two further tests are to follow, the CMAI, which measures agitated behavior [48, 49], and the NOSGER, which covers clinically relevant behavior of psychiatric disorders of old age [50, 51]. Based on the results of these tests, it is decided whether the case can be assessed as yellow or whether it is a red case (acute crisis).

Depending on the respective category, the case manager proceeds differently: In green cases, the case manager offers information on regional support options and sets a next appointment for six months later. In yellow cases, the case manager provides more intense care contacting the patient at least once a month. In red cases, the case manager calls in the outpatient clinic that consists of specialized nursing staff, a psychiatrist, and a social worker. The outpatient clinic continues to provide care until the crisis is overcome. To this end, the outpatient clinic offers home visits of the appropriate frequency to avoid hospitalization. If it is mandatory, an inpatient stay in a geriatric psychiatric clinic is initiated.

Throughout the course of DemStepCare, this risk stratification is regularly repeated (at least at t0, t1, and t2, and invididually if needed) and appropriate action is taken to ensure that each patient receives the care he or she needs. Figure 2 shows an overview of the described procedure.

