**Fig. 2 Fig2:**
[figure not shown]
Overview of the DemStepCare intervention (medication analyses by the pharmacy and communication via the electronic case record are not shown to ensure clarity)

In addition, clinical pharmacists regularly conduct structured medication reviews with the aim of improving the quality and safety of the drug therapy. The attending GPs are alerted to inappropriate medication and drug-related problems (DRP).

Communication between the different parties (i.e. GPs, case managers, outpatient clinic, pharmacy) takes place via a specifically adapted electronic case record. Thus, timely and effective communication is facilitated.

While participating in DemStepCare, patients continue to be cared for by their GPs, who can repeatedly take part in dementia-specific training sessions as the project progresses.

#### Description of control condition 1

GPs assigned to the control group 1 receive a shorter form of training. A case manager is employed and risk stratification is conducted, too, but the result has no influence on the further treatment of the patients, i.e. it only serves evaluative purposes. Neither the GPs nor the patients get to know the result of the stratification. There is a follow-up meeting with the case manager after nine months.

As there are small elements of intervention in control condition 1, control condition 1 cannot be considered as being merely usual care. However, the training of the GPs is intended as an incentive and the visits of the case managers are necessary to gather data for the evaluation. We therefore decided to use this slightly expanded usual care condition as control condition 1. Control group 2, the historical control condition, is inherently usual care.

Training of the GPs in intervention as well as in control condition 1 is carried out by experienced healthcare professionals. The case managers also receive training resulting in a certification as case manager according to the German Society for Care and Case Management (in German: Deutsche Gesellschaft für Care und Case Management, DGCC).

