#### Secondary endpoints relating to GPs

All participating GPs take part in a panel survey. Here, attitudes, self-efficacy, experienced competence, commitment, and perceived challenges with regard to the diagnosis and treatment of dementia are investigated. We use the term “dementia sensitivity” for this complex, heterogeneous bundle of attitudes and experienced abilities. The questionnaire that we developed especially for DemStepCare is based on our previous experience in this field [10, 58, 59]. In the case of the GPs, there are three measurements: one at baseline (t0_GP_), i.e. before randomization and the first training session of the GPs, one 12 months after completion of the first training (t1_GP_), and one at the end of the intervention phase (t2_GP_).

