#### Recruitment of patients and their caregivers

Patients who are potentially eligible to participate in DemStepCare are contacted by their GPs. If possible, their caregivers are also addressed. Those who agree to join the study are assigned to either the intervention or control group 1, based on the group membership of their respective GP.

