### Limitations

The progress of dementia will vary greatly among the participants. Therefore, some patients may not be able to complete the questionnaires, which might lead to a selective loss of data. Although in many cases we will have access to patient data from caregivers, it may be that they are not able to give an evaluation without bias. Past research has found differences between the evaluation of the quality of life of PwD made by PwD themselves and by caregivers, with caregivers usually evaluating the patients’ quality of life more negatively [76–78]. Therefore, proxy assessments in this area cannot be seen as a substitute for self-assessments and must be interpreted with caution.

Even though GPs are a central part of DemStepCare, only a small percentage of GPs are able to be personally interviewed. Of course, all GPs are covered by the panel survey. Nevertheless, it would be interesting to interview this target group individually to obtain information that is more specific.

Other weaknesses concern the recruitment of and by GPs: As GPs participate in the program voluntarily, all participating GPs are likely to be particularly interested in dementia. So there is a certain selection bias, leaving it unclear how the program works for less committed GPs. Since PwD in control group 1 benefit only marginally from DemStepCare, GPs in control group 1 may be less motivated to include patients than GPs in the intervention group. This could lead to different numbers of patients being recruited per group.

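### GPs who know their arm enrol patients after randomisation, so the arms are liable to differ in case mix; the primary models cover this only in part, and least for hospital days

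*Protocol article*

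**What the plan says.** All references are to the protocol article.

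- **Order of events.** Under *Trial design*: "Randomization with a 1:1 ratio is undertaken at the level of GPs’ practices and stratified by dementia sensitivity of the GPs". Under *Secondary endpoints relating to GPs*, the first GP survey is "one at baseline (t0_GP_), i.e. before randomization and the first training session of the GPs". Under *Description of the intervention condition*, enrolment follows training: "The so trained GPs enroll patients and if possible their caregivers in the study program".
- **Who selects patients.** Under *Recruitment of patients and their caregivers*: "Patients who are potentially eligible to participate in DemStepCare are contacted by their GPs". Those who agree "are assigned to either the intervention or control group 1, based on the group membership of their respective GP".
- **Training by arm.** In the intervention arm, "GPs are to identify dementias earlier and become more confident in dealing with the diagnosis". Under *Description of control condition 1*: "GPs assigned to the control group 1 receive a shorter form of training". The content of the shorter course is not given.
- **Who is eligible.** Both existing and newly made diagnoses qualify. There is no severity criterion, but nursing-home residents and people without basic capacity to consent are excluded.
- **Primary models** (*Statistical methods*). All three have random practice effects, adjustment for GP dementia sensitivity and an allowance for the COVID-19 break. Quality of life and caregiver burden are also adjusted for their own baseline. Hospital days are analysed by negative binomial regression with no baseline term stated, although *Primary endpoints* says the item is asked at t0 and t1.
- **Acknowledged limitation.** Lower motivation of control GPs to recruit is discussed, with one consequence drawn: "This could lead to different numbers of patients being recruited per group".

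**The concern.** Randomising practices balances the practices and the patients they already have. It does not balance a patient sample assembled afterwards by people who know the allocation. Here the recruiters have also been trained differently, and one aim of the longer training is to change when dementia is recognised. If patients at different stages enter the two arms, quality of life, caregiver burden and hospital use at t1 can differ for reasons unrelated to the care model. All three primary comparisons are exposed. The limitations section recognises that the numbers recruited may differ by arm, but not that the patients may differ.

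**Working it through.** **1. Can the mechanism operate?** It needs four conditions, and the article meets each:

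- Allocation precedes patient selection: the GP survey comes before randomisation and training, and trained GPs then enrol.
- The selector knows the arm: no blinding of GPs is described, the two arms get different training and services, and the motivation argument under *Limitations* presupposes that control GPs know their group.
- Training differs by arm and bears on diagnosis.
- New diagnoses are eligible, so a change in diagnostic behaviour can change who enters.

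**2. Do the stated safeguards address it?**

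| Safeguard | What it does here |
|---|---|
| Stratification on and adjustment for dementia sensitivity | Uses a score taken before training, so it cannot correct selection that arises after training |
| Design effect and random practice effects | Deal with variance, not with a systematic difference between arms |
| Baseline score (quality of life, burden) | Removes part of an imbalance, but not differences in later progression |
| Hospital days | No baseline term stated |

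**3. The plan's own figures.** With d = 0.30, two-sided alpha 5%/3 and power 0.80, a two-sample t-test needs 234.1, rounded up to 235 per group. The design effect is 1 + 0.01 × 14 = 1.14, and 235 × 1.14 = 267.9, rounded to 268. Both figures reproduce, so the point does not rest on an arithmetic error.

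**4. Illustration of size.** The article gives no stage imbalance and no relation between stage and outcome, so the inputs are assumptions. Suppose the share of newly diagnosed patients differs by 10 to 30 percentage points between arms, and new and known cases differ by 0.3 to 0.5 SD on the outcome.

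- Shift b = difference in share × SD gap. Range: 0.10 × 0.3 = 0.03 to 0.30 × 0.5 = 0.15 SD, or 10% to 50% of d = 0.30. At 20 points: 0.06 to 0.10 SD.
- SE = √(2 × 1.14/n): 0.0654 for n = 533 (expected patients) and 0.0801 for n = 355 (expected caregivers).
- Chance of rejection with no true effect = P(|Z + b/SE| > 2.394), where 2.394 is the two-sided 1.67% critical value.

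With baseline adjustment, assume also that the arm gap is the same at t0 and t1 and that scores at the two times correlate at r = 0.5 to 0.7. The shift becomes b(1 − r) and the SE becomes SE × √(1 − r²), so the ratio b/SE is multiplied by √((1 − r)/(1 + r)): 0.577 at r = 0.5 and 0.420 at r = 0.7.

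| n per group | b (SD) | Unadjusted | Adjusted, r = 0.7 | Adjusted, r = 0.5 |
|---|---|---|---|---|
| 533 | 0.06 | 7.0% | 2.5% | 3.3% |
| 533 | 0.10 | 19.4% | 4.1% | 6.6% |
| 355 | 0.06 | 5.1% | 2.2% | 2.7% |
| 355 | 0.10 | 12.6% | 3.3% | 4.8% |

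The nominal rate is 1.67%. The unadjusted column matches none of the planned models: quality of life and burden are baseline-adjusted, and hospital days is a count analysed on another scale. The adjusted columns are closer to the two score endpoints. For hospital days the article gives nothing from which to calculate a figure.

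**The case against.** The strongest reply is that an imbalance is possible but not shown. The control training is not described, so the gap in diagnostic teaching cannot be sized. Patients with existing diagnoses enter both arms, and the consent and nursing-home rules limit severe cases in both. This stands.

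A reader might infer that the intervention arm will hold earlier cases and that the bias therefore favours the intervention. The documents do not support that as a conclusion. Intervention GPs can offer at least monthly contact in higher-risk cases and a crisis outpatient clinic, which is a reason to enrol the most burdened families. The article itself expects control GPs to be less motivated to include patients. Selection could therefore run the other way.

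A second reply is that further covariates and sensitivity analyses may sit in an analysis plan that is not shown, and *Statistical methods* does not call its list complete. This stands in part. The section does name adjustments endpoint by endpoint and gives a baseline term to two of the three. The recruitment order and the limitation confined to numbers are also statements in this article, not gaps left to another document.

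A third reply is that the obvious covariates may be unavailable or unsuitable. Of the candidates, only the hospital-days item and the DSV are documented at t0. Date of diagnosis, age and sex are not stated as collected. The DSV rates the home-care situation, so it is only a partial proxy for severity. New versus known diagnosis can itself be changed by the training, so adjusting for it in the primary model is debatable. These points stand and shape the fix.

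**Conclusion.** The point holds as a risk of recruitment bias of unknown direction and size. Patients are selected after allocation by GPs who know their arm and are trained differently in a way that bears on diagnosis, and the named adjustments do not fully cover a resulting difference in case mix. Quality of life and caregiver burden are partly protected by their baseline terms. Hospital days is the most exposed.

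The unadjusted rates of about 7% to 19% (533 per group) and 5% to 13% (355 per group) could be read as the trial's expected error rates. They are not: they illustrate an unadjusted comparison of means under an assumed 20-point difference and a 0.3 to 0.5 SD gap. Under the further assumptions of an equal gap at t0 and t1 and a correlation of 0.5 to 0.7, they fall to about 3% to 7% and 2% to 5%. None of these figures applies to the count endpoint. The article should be amended, but nothing in it shows that the comparison will be biased by any particular amount.

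**What to change.** 1. Add the t0 hospital-days item to the negative binomial model.
2. Add the t0 DSV result, recorded by case managers in both arms, to all three primary models, described as a partial proxy for severity. Add age and sex if they are recorded.
3. Pre-specify a sensitivity analysis restricted to patients diagnosed before their practice was randomised, if the diagnosis date is available. Keep new versus known diagnosis out of the primary model.
4. Compare baseline case mix by arm: t0 scores, t0 hospital days, DSV and, if recorded, the share newly diagnosed.
5. Extend the *Limitations* text from different numbers to different patients.

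If the full analysis plan already contains items 1 to 4, it is enough to say so.

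The cost is small: items 1 and 2 rest mainly on data already planned for t0, and items 3 and 4 add one analysis and one table. The restricted analysis uses fewer patients. Together these steps reduce the bias but do not remove it, because the GPs' choice of whom to invite remains unblinded even among patients with existing diagnoses. Listing eligible patients before allocation would act at the source. However, the intervention was already being delivered before its suspension in April 2020, and the article does not say whether any practice was still to be randomised.
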